## Abstract

**Background:**

Chronic hepatitis B virus infection (HBV) is an important health problem in the Turkish community in the Netherlands, and promotion of screening for HBV in this risk group is necessary. An individually tailored intervention and a culturally tailored intervention have been developed to promote screening in first generation 16-40 year old Turkish immigrants. This paper describes the design of the randomized controlled trial, which will be used to evaluate the effectiveness of the two tailored internet interventions as compared to generic online information on HBV, and to assess the added value of tailoring on socio-cultural factors.

**Methods/Design:**

A cluster randomized controlled trial design, in which we invite all Rotterdam registered inhabitants born in Turkey, aged 16-40 (n = 10,000), to visit the intervention website is used. A cluster includes all persons living at one house address. The clusters are randomly assigned to either group A, B or C. On the website, persons eligible for testing will be selected through a series of exclusion questions and will then continue in the randomly assigned intervention group. Group A will receive generic information on HBV. Group B will receive individually tailored information related to social-cognitive determinants of screening. Group C will receive culturally tailored information which, next to social-cognitive factors, addresses cultural factors related to screening. Subsequently, participants may obtain a laboratory form, with which they can be tested free of charge at local health centres. The main outcome of the study is the percentage of eligible persons tested for HBV through to participation in one of the three groups. Measurements of the outcome behaviour and its determinants will be at baseline and five weeks post-intervention.

**Discussion:**

This trial will provide information on the effectiveness of a culturally tailored internet intervention promoting HBV-screening in first generation Turkish immigrants in the Netherlands, aged 16-40. The results will contribute to the evidence base for culturally tailored (internet) interventions in ethnic minority populations. An effective intervention will lead to a reduction of the morbidity and mortality due to HBV in this population. This may not only benefit patients, but also help reduce health inequalities in western countries.

**Trial Registration:**

The Netherlands National Trial Register NTR 2394.

## Background

Hepatitis B virus infection (HBV) is one of the major infectious diseases in the world [1]. Each year, around 1,800 HBV infections, 79% of which are chronic, are reported in the Netherlands [2]. Chronic HBV infections cause 23% of all liver cancers in the Netherlands, and are an important problem in the Turkish community, which is the Netherlands' largest group of immigrants from non-industrialized countries [3,4]. While this community represents 8% of the total city population in Rotterdam (with 45,415 people), it accounts for 30% of reported chronic HBV infections [5]. Seventy percent of reported infections among Turks involve people aged between 16 and 40 years. In this age-category, the mean incidence of reported HBV infections is 122 per 100,000 individuals of Turkish origin, much higher than the 35 infections per 100,000 persons reported in the total population of Rotterdam [6]. However, these figures underestimate the population prevalence: many chronic HBV patients do not have the signs and symptoms of disease, and are therefore not reported. Population-based studies indicate a prevalence of chronic HBV of 0.2% in the general Dutch population, and a much higher prevalence of 2.6 - 4.8% in first generation Turkish immigrants (i.e. those born in Turkey) [4,7-9]. These studies furthermore show that the prevalence of chronic HBV in second generation Turks is similar to the general Dutch population.

The majority of Turkish patients with chronic infection have acquired HBV through infection from mother to child at birth, or through infection at a young age by blood contact with household members [10,11]. Carriers of the virus may infect others by blood contact or, later in life, through sexual contact [12].

In Turkey, every newborn is vaccinated in the first 24 hours since 1998 [13]. Furthermore, adolescent catch-up vaccinations ensured that adolescents up to the age of 16 years had been vaccinated by 2008[14]. Current national HBV-control policies in the Netherlands focus on screening pregnant women and on vaccinating specific risk groups, such as newborns from HBV-infected mothers (since 1989), children with at least one parent from an HBV-endemic area (since 2003), and people with high-risk behaviour (since 2002) [12]. These programmes leave a substantial part of the adult Turkish population in the Netherlands undetected and unprotected regarding HBV. Furthermore, in the past decade, treatment options of chronic HBV have improved [15]. In order to detect individuals eligible for treatment and to prevent transmission, screening for HBV should be promoted through public health interventions targeted specifically in first generation Turkish immigrants.

Tailoring interventions to determinants of health behaviour has proven to be effective in health promotion [16], also related to infectious diseases [17,18], and in promotion of screening participation [19,20]. Relevant social-cognitive determinants for this specific target population, derived from common health behaviour theories, focus group discussions, and a survey questionnaire in the Turkish population in the Netherlands [21,22] ([name] et al.: Social-cognitive and socio-cultural predictors of hepatitis B screening behaviour in Turkish Dutch, submitted), were the low awareness and knowledge regarding hepatitis B and its prevention, and the attitude, self-efficacy, social support and subjective norm regarding hepatitis B-screening in the target population. Up to now, tailored interventions are most often based on such individual factors, also called the proximal determinants of health behaviour. However, these proximal determinants may be dependent on more distal social-cultural factors [23]. These factors ask for 'cultural tailoring' of interventions including cultural traditions, values, and norms in tailored strategies [24,25]. In our previous work regarding the determinants of HBV-screening behaviour, we also identified socio-cultural factors related to HBV-screening. These were shame and stigma regarding HBV, the association of HBV-screening with sexuality, the importance of family values, religious values and rules regarding health, and the level of satisfaction with the Dutch health care.

A relatively easy way of tailoring health information for specific groups is using information and communication technology (ICT) and the Internet. Advantages for health promotion include the interactivity, use of active learning methods, multimedia presentation, temporal flexibility, and low costs relative to its potential population reach [26]. An important condition for success of tailored internet interventions is basic access to the internet. Research in the Netherlands has shown an increase in access to computers and the Internet in the population in general, and in the Turkish community as well [27]. In our survey, we found that 87% of the Turks had a computer at home, and that an equal part of the population used the internet. The majority (90%) of men and the younger women (16-28 years) who used the internet did this daily or at least a few times per week. Seventy-five percent of the women above the age of 28 years said to use the internet frequently. Of the 20% of women in this age group who said not to use internet themselves, about 70% reported to live with someone in the house who did make use of the internet.

The effect of tailoring in behaviour-focussed infectious disease control and the added value of including cultural tailored approaches has not been studied to date. We therefore recently developed two internet interventions aiming to promote screening in first generation Turkish immigrants aged 16 to 40 years, using the Intervention Mapping approach ([name] et al.: Development of a culturally tailored internet intervention promoting hepatitis B screening in the Turkish Dutch community, submitted). Intervention Mapping (IM) describes the stepwise process for the development of theory- and evidence based and practice-based interventions [28].

Tailoring is defined as any combination of information or change strategies intended to reach one specific person, based on characteristics that are unique to that person, related to the outcome of interest, and have been derived from an individual assessment [29]. The individually tailored intervention focuses on social-cognitive determinants of screening behaviour, such as awareness, knowledge, attitude, self-efficacy, perceived subjective norm and support, susceptibility to HBV, and personal norms related to health. Cultural tailoring may be defined as tailoring a health message 'which recognizes and reinforces a group's cultural values, beliefs, and behaviours and built upon those to provide context and meaning to the message about a given health problem or behaviour' [25]. Cultural tailoring is expected to have even more impact on behaviour than tailoring, by paying attention to the embeddedness of human health behaviour in the cultural context and social structure [30]. Cultural sensitivity in tailoring can be conceptualized in terms of two primary dimensions: surface structure and deep structure [25]. We used surface structure elements in order to increase the comprehension and acceptance of messages, by matching intervention materials and messages to characteristics of the target population, such as the language and role models preferred by the target audience. We used deep structure elements to convey salience, by understanding how members of the priority population perceive the cause, course, and treatment of hepatitis B, as well as how they perceive the determinants of the desired screening behaviour. We addressed factors such as religion and family values that influence screening behaviour. A detailed description of the intervention is described elsewhere ([name]: Development of a culturally tailored internet intervention promoting hepatitis B screening in the Turkish Dutch community, submitted).

This study aims to evaluate the effectiveness of the two tailored internet interventions as compared to generic online information on HBV, and to assess the added value of additional tailoring on socio-cultural factors.

## Methods/Design

### Study design

We apply a cluster randomised controlled trial to study the effect of the individually tailored internet intervention (group B) and the culturally tailored internet intervention (group C) on screening behaviour, compared to generic online information (group A). Measurements of screening behaviour (i.e. being screened for HBV (yes/no)) and of the determinants of this behaviour will be at baseline and one month post-intervention.

### Study population

The study population consists of 16-40 year-old citizens of Rotterdam, born in Turkey. Excluded from the study are those:

- not registered in the municipal population registers (MPR)

- aware of having been tested, and knowing to be a carrier of HBV

- aware of having been tested, and being immune

- aware of having been fully vaccinated

### Recruitment of the study population

From the municipal public registration (MPR) we will retrieve names and address details of all persons aged 16-40 years (as per 1 September 2010) who are first generation Turkish immigrants. All subjects will be provided with a unique client ID, which we have randomly assigned to one of the three intervention groups. Respondents will be recruited to visit the website by means of a personal invitation by postal mail. The invitations will be sent out from 13 September to 17 December, 2010. This period was chosen because of the end of the Ramadan on 9 September, 2010. The planning will ensure that all persons living at the same house address will receive the invitation on the same day. Simultaneously, an information campaign in the Turkish community in Rotterdam will be conducted, using newspapers, local radio, community-based organisations and key figures in the Turkish community. Additionally, respondents will be recruited through links on websites with general health information and websites directed specifically at the Turkish community.

In the personal invitation, the addressees will be referred to the internet. On the homepage of the project a short explanation of the health problem of HBV is given, together with information about the facilities provided at the website. Visitors of the website are only able to log in on the website by using their client ID provided in the personal invitation. The website will be offered bilingually, i.e. the visitor may choose between the Dutch or Turkish language. Visitors will then be guided through some exclusion questions in order to select persons eligible for testing (see exclusion criteria).

### Randomisation and exposure to the intervention

All persons living at the same address (i.e. family members or house-mates), will be assigned randomly to one of the three research groups: standard information (group A), individually tailored information (group B) and culturally tailored information (group C). Participants in the control (group A) and intervention groups (groups B and C) are thus enrolled in the same way. Those who enter the internet page and show to be eligible for testing will be questioned for demographic information and asked for a current email address for participation in a follow-up questionnaire. When participants stop during the internet session, and log in using their client ID later on, they will continue in the same group.

During the intervention, participants provide information on both social-cognitive and socio-cultural determinants by answering questions on their beliefs and expectations regarding hepatitis B screening. This information and the provided demographic data will be linked to the client ID and saved in a database. At the end of the information session or tailored intervention, participants may choose to receive a laboratory form either by email or post. Prior to receiving the form, they will receive client information, in which the procedure of testing, possible results of the test and follow-up is explained. Participants will then be asked to sign a checkbox for informed consent. Participants are also asked to co-operate in a follow-up questionnaire about the website one month after the date of first website visit. The laboratory form will be either sent by email or mail, and the client information is once more included. When the participant is younger than 18 years at the date of printing the form, a signed consent from the parents is needed on the form. In that case, information for the parents will be included in the client information. For individuals unable to use the internet, we will provide the laboratory form with generic information on HBV on request by postal mail. However, these individuals are excluded from the research population, as they are not exposed to one of the three interventions.

### Test site (location for blood sampling)

Test sites (n = 85) are community health centres conveniently located in the neighbourhoods where participants live. The blood samples will be analysed according to a predefined standard test algorithm (see Figure 1). The laboratory will inform the Municipal Public Health Service (MPHS) about the test result by providing client ID, date of birth, postal code and test results.

**Figure 1 F1:**
[figure not shown]
**Standard test algorithm for Hepatitis B screening in Turkish Dutch**.

### Follow-up actions

All HBc-negative results (indicating that persons have not been in contact with the virus) can be sifted out by non-medical staff of the MPHS. All HBc-postive results will be assessed by a medical doctor. Accordingly, all test results will be entered into the client registration system of the MPHS based on name of the person (which may be retrieved using the client ID). This client registration system will automatically distribute a standard letter with the results to the participant. The four possible outcomes of the test are: (1) being susceptible to HBV; (2) being immune for HBV due to previous infection; (3) being a HBV carrier, already registered with the MPHS; (4) being a carrier, not registered with the MPHS yet (see Figure 1).Susceptible persons will be informed about their test result, and will be advised to be vaccinated (at a reduced rate) at the MPHS. Immune persons are informed about their test result and the fact that no further action is required. MPHS registered carriers will be informed about their result, and that no further action is required as they have received adequate care in the past. Non-registered carriers will be informed about their status, and will be requested to visit the MPHS for a counselling session and a second blood sample for determination of the liver function through an ALT test. Elevated ALT levels indicate liver inflammation, and these participants will be referred to a medical specialist. In case of normal ALT levels, the participants are referred to their GP for a yearly check-up. In all letters, a telephone number for additional questions is provided. Figure 2 represents the project's flow-chart, indicating the flow from the moment the participant logs in on the project website, through a visit to the community health centre for blood sampling, and the remaining procedure at the MPHS once the test result is known.

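### The message planned for registered carriers says nothing more is needed because of past care, and as stated gives no advice to keep up yearly check-ups

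*Protocol article*

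**What the plan says.** The Follow-up actions section of the protocol article lists four possible test outcomes. The third is "being a HBV carrier, already registered with the MPHS" and the fourth is a carrier not yet registered.

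- **Registered carriers** are given their result and told that "no further action is required as they have received adequate care in the past". No ALT test, referral or check-up is described for them.
- **Non-registered carriers** are asked to come to the MPHS for counselling and an ALT test. Those with elevated ALT go to a specialist. For the rest: "In case of normal ALT levels, the participants are referred to their GP for a yearly check-up".
- **Immune persons** are also told that nothing further is needed, in the same terms as registered carriers but without the clause about past care.

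On delivery, every HBc-positive case is reviewed, since these "results will be assessed by a medical doctor". After the results are entered, "This client registration system will automatically distribute a standard letter with the results to the participant". One element is common to all outcomes: "In all letters, a telephone number for additional questions is provided".

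**The concern.** A yearly check-up is a continuing need. The article applies it to newly found carriers whose ALT is normal, so by its own standard a carrier without liver inflammation still needs watching. The reason given for asking nothing of registered carriers is care already received, and that does not show that monitoring is going on now.

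The message also gives registered carriers the same instruction as people who have cleared the infection. A reader of such a letter could reasonably conclude that check-ups can stop, or need not be restarted if they have lapsed.

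What is at stake is participant safety after the test. The primary outcome is whether a person was tested, and this message follows the test result, so the trial's comparison is not touched.

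**Working it through.** The article gives no figure for this point. The check is a comparison of the stated routes, followed by a rough count.

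**1. The two carrier routes side by side (Follow-up actions).**

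| | Registered carrier | Non-registered carrier, normal ALT |
|---|---|---|
| Told the carrier result | Yes | Yes |
| New counselling and ALT | None described | Yes |
| Stated continuing care | None | Yearly GP check-up |
| Reason given | Adequate past care | Normal ALT found now |

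The routes agree if past care included a referral for yearly check-ups that still stands. The article neither says this nor rules it out. Under either reading, the stated message does not tell the carrier that check-ups go on.

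**2. Can current follow-up be assumed for everyone who gets the message?** The Study population section excludes people who know they are carriers, and the Recruitment section applies this through website questions. A registered carrier tested by that route therefore did not report knowing it. The screen is self-reported, and the Background names shame and stigma around HBV, so passing it does not show that a person is unaware of carriage or out of care. It shows only that current follow-up cannot be taken for granted in every case.

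**3. Indirect support in the Background.** The article notes that "many chronic HBV patients do not have the signs and symptoms of disease", so symptoms may not bring a carrier back to care. It also says that "in the past decade, treatment options of chronic HBV have improved", so earlier care may predate newer options. Both statements are made to explain under-reporting and to justify screening undetected people. They are not about registered carriers and carry little weight here.

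**4. Rough count.**

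Inputs:
- 1000 people tested (Sample size section: 200 + 350 + 450 = 1000).
- Prevalence of chronic HBV 2.6% to 4.8% in first generation Turkish immigrants (Background).
- Share of tested carriers already registered: not given. I assume 0-20%.

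Formula: letters = number tested × prevalence × registered share.

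Carriers in all, before the exclusion questions: 1000 × 0.026 = 26, and 1000 × 0.048 = 48.

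| Registered share (assumed) | Letters at 2.6% | Letters at 4.8% |
|---|---|---|
| 0% | 0 | 0 |
| 5% | 1.3 | 2.4 |
| 10% | 2.6 | 4.8 |
| 20% | 5.2 | 9.6 |

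If only 500 were tested (assumption): 500 × 0.026 = 13 and 500 × 0.048 = 24 carriers. A 20% share then gives 13 × 0.2 = 2.6 to 24 × 0.2 = 4.8 letters.

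The prevalence applies before known carriers are screened out, and registered carriers are the ones most likely to be screened out. The true number may be near zero.

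**The case against.** The strongest reply is that the letter is not shown. The article reports its content in one clause, and articles often leave the text of result letters to the full protocol. The two figures, one of which charts the procedure after the result, are also not visible. Silence about check-ups in a summary does not prove that the letter is silent. This stands as a limit. But the point does not rest only on an omission: the article states an instruction and a reason, and that stated instruction is the part that could mislead. If the letter already advises check-ups, the sponsor can close the point by saying so.

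A second reply is that the sentence makes sense as it is. Registration may mean earlier counselling, ALT testing and a referral that still stands, so the new result triggers no new step. This is plausible. A reader might infer that the section contradicts itself by monitoring one group of carriers and releasing the other. The article does not support that inference. What remains is that a carrier with a standing referral could still read the message as leave to drop it.

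A third reply is that safeguards exist: a doctor reviews every HBc-positive result, the letter discloses carriage, and a telephone number is given. All true. They reduce the risk, but someone told that nothing is needed has little reason to call.

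**Conclusion.** The point holds as a minor participant-safety matter of wording and is best labelled a cheap improvement. As stated, the message to registered carriers could suggest that monitoring is unnecessary, while the same section treats carriage with normal ALT as needing a yearly check-up.

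On size, 0 to about 10 people would get the message if 1000 are tested and 0-20% of carriers are registered. The share is my assumption, and the number may be near zero. Confidence is limited because the letter and the figures cannot be seen.

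A reader might go further and infer that registered carriers who reach testing are unaware of their infection, have fallen out of care, or were treated to an outdated standard. The article shows none of these. Nor is there any effect on the primary outcome, the analysis or the power.

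**What to change.** In the message for registered carriers, replace the statement that nothing further is needed with: *No new MPHS work-up is required; please continue, or resume, yearly check-ups with your GP or specialist.*

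The cost is one changed sentence in a standard letter and possibly a few extra GP visits. No added counselling or ALT test at the MPHS is proposed for this group. Making those depend on what the register shows about earlier care would assume record contents that the article does not describe, and would add procedures.
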